### Participant retention {18b}

Plans to promote patient participant retention include tiered gift card incentives, with increasing value over time, as well as multiple reminder contacts via email and telephone to encourage survey completion.

PCP retention is supported through engagement of site-specific clinical champions, provision of CME credit contingent on completion of the full study protocol, and periodic email check-ins.

For patient participants who discontinue or deviate from the intervention protocol, all data collected up to the point of discontinuation are retained. In addition, clinical outcome data continue to be collected via chart abstraction under existing informed consent and HIPAA authorization, even if survey participation ceases.

Loss to follow-up between baseline and 6-month assessments will be monitored, and dropout rates will be compared between study arms. Where follow-up data are missing, multiple imputation techniques will be considered as appropriate, and missing data may alternatively be recorded as a separate category for modeling.

### Data management, security, and quality {5d} {19}

All study data are entered and managed using REDCap, by trained study personnel using standardized electronic forms with predefined coding schemes. Built-in validation rules, including logic checks and range checks, are implemented to promote data completeness and accuracy at the point of entry.

Data quality is overseen by the DCC through routine review for completeness, internal consistency, and cross-site variability. For chart-based data abstraction, standardized training procedures and periodic cross-checks are used to promote inter-rater consistency, with discrepancies resolved through consensus review involving site investigators as needed.

### Confidentiality {27}

All patient and PCP data is housed on site-specific REDCap servers only accessible to respective site’s study team through role-based permissions. To protect confidentiality, patient and provider data are deidentified at the time of entry and labeled only with a REDCap-generated unique study identifier. No direct personal identifiers (e.g., name, medical record number, date of birth) are stored in the analytic dataset.

Linkage between the study identifier and identifiable information, when required for study operations (e.g., recruitment tracking or follow-up), is maintained locally at each site in a secure, access-restricted file and is not shared across sites. Any data shared between sites is deidentified.

### Plans for collection, laboratory evaluation and storage of biological specimens for genetic or molecular analysis in this trial/future use {33}

No biological specimens are collected/evaluated in this protocol.

## Statistical methods

### Statistical methods for primary and secondary outcomes {20a} {20b}

The primary outcome of quality of care will be measured by constructing aggregate QI scores ranging from 0 to 100%, as described by McGlynn et al. [30]. 5% of all records will be re-abstracted to evaluate inter-rater reliability using Gwet’s AC1 correlation [31, 32]. Given the potential differences in patient and provider demographics between the private, public-private, and public county health systems, factors such as patient race/ethnicity, provider sex, and provider specialty will be assessed via a simplified mixed model regression, incorporating random effects to account for clustering. Analysis will be conducted using SAS with significance set at *p* = 0.05.

A chi-square test will be used to compare patient enrollment between health systems to evaluate the potential impact and efficacy of phone vs. email screening as a recruitment tool. Patient referral rate to specialty care in both intervention and routine care arms will be assessed using cluster logistic regression. Appropriate delay of referral is measured as a dichotomous outcome (timely vs. premature referral) with proportion between groups analyzed via a chi-squared test.

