#### Academic detailing

Enrolled PCPs receive academic detailing prior to patient recruitment. This portion of the intervention integrates principles of Educational Outreach, utilizing stepwise application of evidence-based techniques (i.e., baseline knowledge inventories, targeted interventions, etc.) to improve clinical decision-making [16]. First, PCPs complete their baseline UI knowledge assessment via the Pelvic Floor Awareness and Knowledge Survey (PFAKS), a 31-item validated pelvic floor disorder knowledge questionnaire [17]. Once complete, the study team holds an in-person or virtual lecture at intervention practices. Providers unable to attend receive a one-on-one lecture via Zoom. Lectures are led by a UI clinical champion, either a urologist/urogynecologist or PCP from that site who is part of the research team and has expertise in UI management. The lecture centers on a set of thirteen previously developed and tested quality-of-care indicators (QIs) that cover all aspects of non-surgical management of UI, including history and physical examinations (i.e., pelvic exam), urinalysis, initiation of conservative treatment (i.e., lifestyle/behavioral interventions, pelvic floor training, medication, and when to refer to a UI specialist in urogynecology (Table 1)). The QIs were independently developed using the RAND Appropriateness, or Delphi, Method [13] and are validated for use in a diverse population [8, 18, 19]. PCPs also receive a pocket guide with a treatment algorithm.

Within a month after the lecture, UI specialists provide individualized coaching for intervention PCPs. This includes a one-on-one review of the PCP’s baseline quality of care for UI, as measured by retrospective chart abstraction of up to 5 previous UI encounters. Baseline charts are identified by a diagnosis code for UI (Appendix A). After reviewing prior care, the UI specialist offers individualized recommendations. Intervention PCPs are then ready for patient recruitment. Baseline chart abstraction is also performed in the routine care cohort, although without the individualized coaching sessions.

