### Outcomes {12}

#### Primary outcome: quality-of-care measures

The primary outcome of this trial is provider quality of care. Provider quality of care in both arms is measured via retrospective chart abstraction at baseline and again for each respective patient participant. Care provided over a 6-month timeframe is evaluated for adherence with 13 primary care UI QIs we previously developed, to allow adequate time to comply with the QIs [8] (Table 1). For each chart abstraction, a given eligible indicator is scored as a dichotomous measure (met vs. not met). Aggregate scores are measured as proportions: encounters where patients receive the recommended care vs. total encounters where patients are eligible for specific QIs. The results will be reported as percentages ranging from 0 to 100%.

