### Sample size {14}

All power estimates were performed assuming mixed-model regression modeling to account for the nested study design (patients within providers within offices) using PASS 2020 software [27]. As randomization will occur at the office level, power was computed assuming an average of 3 providers per office with an intra-cluster correlation of 0.04 (consistent with previous reports for process-of-care outcomes [28]) and a correlation of 0.16 across patients within each provider. Preliminary data found the average baseline quality of care to be 40% with a standard deviation of 20% [8, 18]. Therefore, to detect a change of 6% in total scores at an alpha level of 0.05 with 80% power, the study will require at least 720 patients from 48 offices (360 patients from 24 offices per study arm; see Fig. 1).

We conservatively estimate this sample size can detect a minimum odds ratio of 0.52, which is equivalent to a decrease in referral rates from 60 to 44% between the two treatment arms of the study, with 80% power at the 0.05 significance level. For patient-reported outcomes, our preliminary data had an average score of (± SD) of 35 (± 20) for the UDI-6 and 18 (± 20) for the IIQ-7. The study is powered to identify a difference of 6 points or greater in each of the two measures between study arms.

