## Assignment of interventions: allocation

### Sequence generation {16a}

Offices were assigned to study arms using randomization lists generated using Wei’s Urn method (to allow for equal sample sizes). Randomization at the practice level was done for all four sites by the study biostatistician 1:1 to each study arm, stratified by study site and office specialty (family medicine, gynecology, geriatrics, and general internal medicine), using PASS 2020 software [27]. Physicians working within a given practice received the same designation to prevent cross-contamination of intervention materials.

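### The factors named for the primary model include neither the PCP's baseline QI score nor study site, so available precision is forgone; the planned 80% power does not depend on it.

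*Protocol article*

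**What the plan says.** The analysis text for the primary outcome (Statistical methods for primary and secondary outcomes) states that "factors such as patient race/ethnicity, provider sex, and provider specialty will be assessed via a simplified mixed model regression", with random effects for clustering. It gives differences between the health systems as the motive. Neither the baseline QI score nor site is named as a term.

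Other sections show that both are available:

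- **Baseline score.** Under Primary outcome, quality of care in both arms is "measured via retrospective chart abstraction at baseline and again for each respective patient participant". Academic detailing says that up to 5 earlier UI encounters per PCP are abstracted, in routine care as well, and that these charts are found by diagnosis code.
- **Site.** Under Sequence generation, offices were randomized 1:1, "stratified by study site and office specialty". In the analysis, site is otherwise used for subgroup analyses (Methods for additional analyses).
- **Target effect.** Sample size sets out "to detect a change of 6% in total scores at an alpha level of 0.05 with 80% power", from a baseline mean of 40% and SD of 20%.

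**The concern.** With 48 offices and about 3 PCPs in each, variation between offices and between PCPs makes up much of the variance of the arm comparison. A PCP's own earlier score on the same indicators is a natural predictor of that variation, and it has already been collected in both arms. Site was important enough to stratify on. If it is left out of the model, between-site variance stays in the office term and the standard error is larger than it need be.

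The documents also leave the role of baseline unclear. It is described alongside the primary outcome, it is not mentioned in the analysis text, and the sample-size section speaks of a change. What is at stake is precision, and a clear statement of which comparison is primary.

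**Working it through.** **Inputs from the protocol article.** Difference 6 points, SD 20, alpha 0.05 (two-sided assumed), power 80%, 24 offices per arm, 3 providers per office, office ICC 0.04, within-provider correlation 0.16 (Sample size); 15 patients per office (Abstract), hence 15/3 = 5 per provider; up to 5 baseline charts per PCP (Academic detailing).

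**Step 1: reproduce 720.**
- Independent patients: 175 per arm.
- Design effect: 1 + (5 − 1)(0.16) + 5(3 − 1)(0.04) = 2.04.
- 175 × 2.04 = 357 per arm; 357/15 = 23.8, so 24 offices and 360 patients per arm, 720 in total.

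This is a comparison of two arm means at the full SD, with no credit for covariates. Reading the provider correlation as 0.04 + 0.16 = 0.20 gives 780 and does not reproduce.

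**Step 2: unadjusted power.** As shares of the total variance, office is 0.04, provider within office is 0.16 − 0.04 = 0.12, and residual is 0.84.
- Variance of an office mean: 0.04 + 0.12/3 + 0.84/15 = 0.136.
- Standard error of the arm difference: 20 × √(2 × 0.136/24) = 2.13 points.
- Power: Φ(6/2.13 − 1.96) = 80.5%. With a t reference on 46 df it is 78.8%.

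**Step 3: add the baseline score.** Let r be the correlation between true quality at baseline and at follow-up, taken as equal at office and provider level. The documents do not give r. With k baseline charts per PCP:
- Variance of the baseline office mean: 0.08 + 0.84/(3k), which is 0.136 for k = 5 and 0.173 for k = 3.
- Covariance with the follow-up office mean: 0.08r.
- Variance ratio after adjustment: 1 − (0.08r)²/(0.136 × baseline variance), which is 1 − 0.346r² for k = 5 and 1 − 0.271r² for k = 3.

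| r (assumed) | Ratio, 5 charts | Power, 5 charts | Ratio, 3 charts | Power, 3 charts |
|---|---|---|---|---|
| 0.3 | 0.969 | 81.7% | 0.976 | 81.4% |
| 0.5 | 0.913 | 83.9% | 0.932 | 83.1% |
| 0.7 | 0.830 | 87.1% | 0.867 | 85.7% |
| 0.9 | 0.720 | 91.3% | 0.780 | 89.1% |

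These are normal-approximation figures, to be set against 80.5%. A calculation that applies the reliability of a single PCP's 5-chart mean, 0.16/(0.16 + 0.84/5) = 0.488, to the office and provider variance gives 83.3%, 86.0% and 89.6% for r of 0.5, 0.7 and 0.9. The direction is the same and the size similar.

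**Step 4: add site alone.** If site explained 25% or 50% of the office variance (assumed), the office-mean variance would fall to 0.126 or 0.116, and power would be 83.3% or 86.2%.

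**Step 5: covariate or subtraction.** Subtracting a 5-chart baseline gives an office-level variance of 2(0.136) − 2(0.08r) = 0.272 − 0.16r. Power is then about 66%, 74% and 83% for r of 0.5, 0.7 and 0.9. For the first two values this is worse than ignoring baseline. It is also below covariate adjustment throughout.

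**The case against.** The strongest reply is that this is a condensed article, that its analysis plan is not shown, and that a full covariate list belongs in that plan. Several parts of this stand:

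- A reader might infer that the plan excludes baseline and site. It does not. The list opens with *such as*, and the sentence names no arm term either, so it is not a complete model.
- A reader might infer that the stratification is ignored altogether. Specialty is named (as provider specialty), and differences between the health systems are the stated motive for the model. Only site is missing as a named term.
- A reader might infer that the trial is underpowered or its test invalid. Step 1 shows that 720 takes no credit for adjustment, and leaving out a stratification factor generally makes the test conservative.
- A reader might infer from "to detect a change of 6% in total scores" that a change score is planned. No section prescribes one, and the arithmetic is that of a between-arm difference.
- A reader might extend the point to the UDI-6 and IIQ-7. The statistical methods section states no model for patient-reported outcomes, so nothing there can be faulted.

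The size is also open to challenge. Baseline charts are found by diagnosis code, while trial patients come through a screening survey for new or worsening bothersome UI. Intervention PCPs are also coached on those same baseline charts. Both features argue for the lower correlations, and up to 5 charts means that some PCPs will have fewer.

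What survives is narrower. The article names some factors and passes over the two with the clearest claim: one measured in both arms on the outcome's own indicators, the other used to stratify. That is a concrete and better choice of model, and more than a request for detail.

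**Conclusion.** The point holds as a free improvement to the primary analysis. Baseline QI score and site are available and not named, and adding them should increase precision. The direction is secure; the size is not.

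The range of about 82–91% (5 charts, r of 0.3 to 0.9), against 80.5% unadjusted, rests on an assumed r, equal cluster sizes, 5 patients per provider and a normal approximation. With 3 charts it is about 83–89% for r of 0.5 to 0.9. Any gain from site would come on top, but its share of variance is likewise not in the documents. The 5 patients per provider are those implied by the sample size. The Participant timeline closes recruitment at 10–13 per provider, and if every PCP reached that, unadjusted power would already be 88.5–90.3%.

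**What to change.** State the primary model before outcomes are compared by arm:

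- **Outcome:** patient-level 6-month QI score.
- **Fixed effects:** arm, site, office specialty, and PCP baseline QI score (own value and office mean).
- **Random effects:** office, and provider within office.
- **Test:** the arm coefficient, with small-sample degrees of freedom.
- **Sparse baseline:** a simple rule, such as a fixed imputed value, for PCPs with few or no baseline charts.

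Enter baseline as a covariate and do not subtract it. The baseline and trial charts are ascertained differently, and Step 5 shows the cost in power. In Sample size, replace the wording about a change of 6% with a between-arm difference of 6 percentage points in the 6-month score, which is what gives 720.

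The cost is wording in the analysis plan and one phrase in the sample-size section. No new data are needed. The extra terms use a few office-level degrees of freedom out of 48 offices.

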## Methods

### Study setting {9}

The present study is a cluster randomized design with a target of 48 offices in Southern California from 4 academic health systems: one private, two public-private, and one public county health system.

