### Recruitment {15}

Prior to PCP recruitment, the study team met with health system and primary care leadership at each participating site to identify and select eligible primary care offices, with permission from health system, primary care, and practice leadership. Eligible PCPs that wished to participate were then recruited by the study team during individual office meetings.

For patient recruitment, a data analyst generates a weekly list of adult women with upcoming appointments in the next 10–14 days. One week before the scheduled appointments, the research team emails eligible patients the screening survey. Patients who answer that they (1) have new or worsening bothersome UI that they would like to address with their PCP and (2) have not been seen by a urologist or urogynecologist for UI in the past 2 years are then presented with the consent form from the same screening survey.

Because this is a pragmatic trial, variation in screening is allowed based on the population served. For example, to improve recruitment from a safety-net hospital with a large Spanish-speaking patient population with varying internet access, participants from this health system are recruited via a telephone-based screening performed by a fluent Spanish-speaking research team member.

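### As described, telephone screening belongs to one health system, so a chi-square test of enrolment between systems cannot show the impact or efficacy of phone versus email screening

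*Protocol article*

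**What the plan says.** In the protocol article, Statistical methods for primary and secondary outcomes {20a} {20b} states the test: "A chi-square test will be used to compare patient enrollment between health systems". Its purpose follows in the same sentence: "to evaluate the potential impact and efficacy of phone vs. email screening as a recruitment tool".

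Study setting {9} says that the offices come "from 4 academic health systems: one private, two public-private, and one public county health system".

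Recruitment {15} gives the general procedure: "the research team emails eligible patients the screening survey". It then says that "variation in screening is allowed based on the population served" and gives one case. The reason for it is "to improve recruitment from a safety-net hospital with a large Spanish-speaking patient population with varying internet access", and the arrangement is that "participants from this health system are recruited via a telephone-based screening performed by a fluent Spanish-speaking research team member". The article describes telephone screening in no other system, no random assignment of mode, and no mix of modes within a system.

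**The concern.** The test compares health systems, but the conclusion it is meant to serve is about screening mode. If mode changes only when the system changes, a difference in enrolment could come from the phone call, the population, the language of contact, live contact with a staff member, or anything else particular to that system. The test gives the same p-value in every case.

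At stake is a prespecified analysis that could lead to a published statement on how well telephone screening recruits women in a safety-net, largely Spanish-speaking setting. The Discussion makes recruitment of that group a priority, so such a statement would be noticed.

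**Working it through.** The article gives no rate, power or sample size for this comparison, so there is no figure to reproduce. The check has three steps.

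**1. Can mode be separated from system?**

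Inputs: four systems (Study setting {9}); phone in one and email in the others (Recruitment {15}, read as described).

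| System | Screening mode as described |
|---|---|
| Private | Email |
| Public-private, first | Email |
| Public-private, second | Email |
| Safety-net (taken here as the public county system) | Phone |

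A model with one indicator per system and one for phone has 4 + 1 = 5 columns. The phone column is identical to the indicator of the one system that uses it, so the rank is 4. The phone effect is fully aliased with that system. The result is the same whichever of the four is the safety-net system, and it needs no assumed rates.

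**2. Is the aliasing harmless because the systems are otherwise alike?**

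The article suggests not. The phone route was chosen because of language and internet access, both of which may affect enrolment under either mode. It also brings a live, Spanish-speaking staff member into the contact, so mode, language support and personal contact change together. The same statistical section anticipates that systems differ: "Given the potential differences in patient and provider demographics between the private, public-private, and public county health systems".

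Read as enrolled versus not enrolled across four systems, the test has (2 − 1) × (4 − 1) = 3 degrees of freedom. Part of that statistic comes from contrasts among the three email systems, which carry no information on mode.

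**3. How easily would the test mislead? (illustration on assumed inputs)**

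The article gives neither the number screened per system nor the enrolment rate. Assume 500 to 3,000 screened per system, an average enrolment of 5% to 20%, no true phone effect, and systems that vary on the logit scale with a given SD. For scale: at 10% enrolment the logit is −2.197. An SD of 0.2 moves it to −1.997 or −2.397, that is, to 1/(1 + e^1.997) = 12.0% or 1/(1 + e^2.397) = 8.3%. Proportion of 1,500 simulated trials per setting with p < 0.05:

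| Between-system SD (logit) | Four-system chi-square | Phone system vs pooled email systems |
|---|---|---|
| 0 | 4.2% to 5.5% | 4.5% to 6.1% |
| 0.1 | 8.4% to 71.0% | 6.4% to 41.1% |
| 0.2 | 24.9% to 94.3% | 15.5% to 66.7% |
| 0.5 | 76.1% to 99.7% | 47.2% to 85.1% |

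With no phone effect at all, modest differences between systems are enough to make the test significant often. The reverse also holds: a real phone effect could be hidden by a system in which enrolment is harder.

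**The case against.** **The safety-net system is only an example.** This stands in part. Recruitment {15} introduces it as an illustration of a general permission to vary screening, and the Discussion speaks of phone-based screening as an addition, which might mean phone on top of email. A reader might infer that phone is certainly used in one system only and that no analysis of the trial's data could ever isolate mode. The article does not support that: mixed use is not described, but it is not excluded. The rank result in step 1 likewise assumes the arrangement as described. The planned test is not rescued, however. Even with mixed use, a comparison between systems would not isolate mode; that would need a comparison within a system that used both.

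**The wording is tentative and the analysis peripheral.** Also fair. The article speaks of potential impact, and recruitment mode is not among the outcomes in Outcomes {12}. That limits the weight, but efficacy is still a causal word tied to a significance test.

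**The detail may sit in an analysis plan.** This does not help. Nothing is missing here: the article states the test, the comparison and the inference, and the inference does not follow.

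**Clustering.** A reader might take the correlations of 0.04 and 0.16 in Sample size {14}, form a design effect, and quote an inflated false-positive rate for this test. The article does not support such a figure. Those values were planned for quality-of-care scores among enrolled patients, not for enrolment among those screened. The screening invitation comes from the research team, not the provider. Any rate would also depend on whether the test has three degrees of freedom, as the four-system wording implies, or one. Only the qualitative remark holds: an ordinary chi-square test makes no allowance for similarity of enrolment within offices.

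**Conclusion.** The concern holds for the plan as described. The between-system chi-square test confounds screening mode with system, population, language and staff contact, and it cannot show the impact or efficacy of phone versus email screening. With four systems it also picks up differences unrelated to mode.

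The conclusion rests on one reading: phone in the safety-net system, email elsewhere, and no mixing within a system. The simulated rates rest on assumed inputs and only illustrate. The effect of office clustering cannot be quantified from the article.

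The weight is minor. A comparison of enrolment between systems is legitimate in itself; only its attribution to mode is unsupported. The primary outcome, the sample size and the comparison of arms are not affected.

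**What to change.** In Statistical methods for primary and secondary outcomes {20a} {20b}:

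- Remove the stated purpose of evaluating the impact and efficacy of phone versus email screening.
- Report screened, eligible and enrolled counts and proportions by health system, descriptively, with each system's screening mode noted. Enrolled counts alone would say little, because Participant timeline {13} closes recruitment at 10 to 13 patients per provider.
- State that mode is confounded with system.
- If a test or interval between systems is kept, present it as a comparison of systems only and allow for clustering by office.

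The cost is the rewording of one sentence and the loss of a mode claim that the data cannot support.

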**Methods:**

In this pragmatic cluster randomized controlled trial, providers across four Southern California healthcare systems are randomized at the office level to receive incontinence intervention (*n* = 24 offices; 72 providers) vs. a non-intervention routine primary care cohort (*n* = 24 offices; 72 providers). The intervention includes (i) academic detailing with physician education and individual performance feedback; (ii) clinical decision support with note templates, order sets, and pop-up EHR alerts; (iii) access to co-management with a dedicated advanced practice provider; and (iv) implementation of an electronic referral service in which a specialist screens referrals for appropriateness. To achieve adequate power, the study will require 720 patients (360 patients per arm, average of 15 patients per office).

The primary provider outcome is the quality of UI care, as measured by adherence to a set of 13 quality indicators (QIs) on a 6-month chart review. Secondary provider outcomes include specialty referral rates (overall specialist referrals and presence of appropriate delay of referral) and disease-specific knowledge measured by the Pelvic Floor Awareness and Knowledge Survey (PFAKS). Patient self-reported outcomes include disease-specific knowledge measured by PFAKS, UI severity measured by the International Consultation on Incontinence Questionnaire (ICIQ-SF) and Urinary Distress Inventory (UDI-6), UI response to therapy measured by Patient Global Impression of Improvement (PGI-I), and patient-perceived shared decision making via the 9-item Shared Decision Making Questionnaire (SDM-Q-9). Patient outcomes are measured at baseline, 3-, and 6-month timepoints post-appointment with the study provider.

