#### Secondary provider outcomes

Data on referral rates are also collected at the 6-month chart abstraction to assess overall specialty referral rates and the presence of an appropriate delay of referrals, in which referrals are placed only after first-line treatment is initiated.

At baseline, providers complete a demographic questionnaire and a modified version of the Pelvic Floor Awareness and Knowledge Survey (Fig. 3). The PFAKS is a 31-item validated questionnaire assessing knowledge of three pelvic floor disorders: pelvic organ prolapse (11 items), stress urinary incontinence (SUI) (10 items), and overactive bladder (OAB) (10 items) with questions on condition pathophysiology, management, and quality of life for these conditions [17]. The modified PFAKS excludes the 11 pelvic organ prolapse items.

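### Appropriate delay of referral is compared between arms with a chi-squared test that ignores clustering, although offices are randomised and the companion referral outcome is analysed with clustering

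*Protocol article*

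**What the plan says.** The section on statistical methods for primary and secondary outcomes deals with the two referral outcomes in consecutive sentences. For overall referral: "Patient referral rate to specialty care in both intervention and routine care arms will be assessed using cluster logistic regression". For timing of referral: "Appropriate delay of referral is measured as a dichotomous outcome (timely vs. premature referral) with proportion between groups analyzed via a chi-squared test". The abstract lists both as secondary provider outcomes, and both come from the 6-month chart abstraction.

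The section on secondary provider outcomes defines an appropriate delay as one "in which referrals are placed only after first-line treatment is initiated". Neither section states a denominator.

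On the design, the section on sequence generation says "Randomization at the practice level was done for all four sites by the study biostatistician 1:1 to each study arm". The sample size section assumes three providers per office, an intra-cluster correlation of 0.04 and "a correlation of 0.16 across patients within each provider". No section applies a cluster adjustment to the timing outcome.

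**The concern.** Patients of one provider, and providers in one office, tend to be managed alike. When whole offices are allocated, that similarity adds to the variance of the difference between arms. An ordinary chi-squared test leaves it out, so the standard error is too small, the p-value too low and any matching interval too narrow. The protocol recognises this for its power calculation, its mixed model and its referral rate, but not for the timing of referral.

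Reducing unnecessary referrals is one of the stated overall goals. Whether referrals came after first-line treatment bears directly on it, so a spurious positive result here could be read as support for the intervention.

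**Working it through.** **Inputs from the protocol article.** Sample size section: 720 patients, 48 offices, 360 patients per arm, three providers per office, correlations 0.04 (office) and 0.16 (provider), SD 20, difference 6, alpha 0.05 (taken as two-sided), power 80%, referral rates 60% and 44%. Abstract: 15 patients per office, hence 15/3 = 5 per provider.

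**Step 1: reproduce the stated sample size.** For independent patients, n = 2 × (1.96 + 0.842)² × 20² / 6², which rounds up to 175 per arm. A patient shares a provider with 4 others and an office, but not a provider, with 10 others, so

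DE = 1 + 4 × 0.16 + 10 × 0.04 = 2.04.

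175 × 2.04 = 357 per arm, against 360 stated; power at 360 per arm is 80.5%. Other readings of the correlations fit worse: office only gives 273 per arm, provider only 287, and a within-provider value of 0.20 gives 385. The design effect of 2.04 therefore matches the protocol's own planning.

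**Step 2: type I error of the unadjusted test, all 720 patients.** The true size at nominal 5% is 2 × (1 − Φ(1.96/√DE)). With DE = 2.04, 1.96/1.428 = 1.372, which gives **17.0%**. A nested binary simulation (20,000 runs per scenario) gave 16.6–17.5%.

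**Step 3: the same test among referred patients only.** If a proportion p is referred at random, DE = 1 + p × (4 × 0.16 + 10 × 0.04) = 1 + 1.04p. If every provider has exactly 5p referred patients, DE = 1 + (5p − 1) × 0.16 + 10p × 0.04.

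| Referred | DE, random numbers | Type I error | Simulated | DE, equal numbers | Type I error |
|---|---|---|---|---|---|
| 44% | 1.46 | 10.5% | 10.5–10.8% | 1.37 | 9.4% |
| 52% | 1.54 | 11.4% | 11.3–11.5% | 1.46 | 10.5% |
| 60% | 1.62 | 12.4% | 12.4–12.7% | 1.56 | 11.7% |

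The range is about **10–12%**.

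**Step 4: vary the correlations.** The protocol gives none for this outcome, so a range is needed (random-numbers formula).

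| Office / provider correlation | 52% referred | All patients |
|---|---|---|
| 0.01 / 0.04 | 6.6% | 8.1% |
| 0.02 / 0.08 | 8.2% | 11.2% |
| 0.04 / 0.16 | 11.4% | 17.0% |
| 0.05 / 0.20 | 13.0% | 19.6% |

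With any positive correlation DE is above 1 and the error above 5%.

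**The case against.** **The test might be a cluster-adjusted chi-squared test, or the analysis plan might settle it.** Adjusted versions exist, and the text does not say unadjusted. But the sentence just before it names a clustered method explicitly, so the natural reading is the ordinary test. The article does not leave the method open; it fixes one that does not suit the design.

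**The correlations were not chosen for this outcome.** This stands. The 0.04 and 0.16 are planning values introduced for process-of-care outcomes. The error rates are therefore conditional, and the range in step 4 belongs with them.

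**A reader might infer both a 17% error and a comparison that randomisation does not protect.** These cannot hold together. The 17% needs all 720 patients, and that comparison is randomised. Loss of protection arises only if referred patients alone are analysed, and the error is then about 10–12%.

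**A reader might take the referred-only denominator as stated.** It is an inference. The two categories have no place for a patient who is never referred, but no denominator is given, and a condensed article may leave it to the analysis plan.

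**A reader might infer that a referred-only comparison would point the wrong way.** It can. With 30 premature referrals per 100 patients in each arm, and total referrals falling from 60 to 44, the premature share rises from 30/60 = 50% to 30/44 = 68%. But this assumes that the intervention removes only timely referrals. The protocol describes specialist screening that sends advice back when first-line care is incomplete, which leans the other way. The example shows what is possible, not an expected bias.

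The other chi-squared test in that section compares enrolment between health systems. It is not a comparison of arms and is no part of this point.

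**Conclusion.** The stated analysis of appropriate delay of referral is wrong as written: it takes no account of office randomisation and is inconsistent with the method fixed for referral rate. This holds whichever denominator is meant.

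The size rests on assumptions: the planning correlations carry over to this outcome, there are five patients per provider, and referral rates lie between 44% and 60%. Stratification by site and specialty could lower the error somewhat, and unequal office sizes would raise it.

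The referred-only problem is conditional. If that is the denominator, the analysis selects on a post-randomisation event that the intervention is meant to change (60% to 44%). If never-referred patients are counted, this second problem falls away and the clustering error is at its largest.

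This should be fixed, but it is not critical. The outcome is secondary, and the primary outcome, the sample size and the referral-rate analysis are untouched.

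**What to change.** 1. Replace the chi-squared test for appropriate delay of referral with the cluster logistic regression already named for referral rate, accounting for both office and provider. This brings the type I error back to about 5%. It needs no new data. Intervals widen by a factor of √DE: under the planning correlations, √2.04 = 1.43 for all patients, or √1.46 = 1.21 to √1.62 = 1.27 among referred patients.
2. State the denominator. If it is referred patients only, report premature referral within 6 months among all enrolled patients alongside, as a supportive analysis. That measure groups never-referred with timely-referred patients, so it is a different quantity and should not silently replace the stated outcome. Redefining the outcome would be more than a wording change in an unblinded trial whose data collection is due to finish by the end of 2025.

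Both changes should be recorded before the outcome data are analysed.
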